### Trial interruption

The trial will be halted should the incidence of clinical endpoints significantly differ between the different devices during the intermediate analysis. The trial will also be halted should the incidence of adverse clinical events exceed the expected values at any point. The incidence of clinical events is under constant observation of the DSMB and CAEC. The principal investigator is continuously informed by the DSMB and CAEC and is, by not being blinded, solely responsible for trial halting.

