## Methods/Design

### Study design and overview

This is a single center, assessor-blinded, randomized study comparing three different stents in *de novo* coronary lesions: the Absorb™, the Promus Element™ and the Biomatrix Flex™. The protocol of the trial has been registered online (NCT01711931) at http://www.clinicaltrials.gov. Figure 1 briefly summarizes the main study steps and Table 1 the longitudinal follow-up. The organization and scientific conduct is supervised by a Steering Committee. A Data and Safety Monitoring Board is responsible for safety and ethical aspects. A Clinical Events Adjudication Committee (CEAC) including interventional and non-interventional cardiologists review and adjudicate all reported events and endpoints and perform computation and angiographic measurements. All members of the CEAC are blinded to the primary results of the trial. The study complies with the Declaration of Helsinki and was approved by the local ethics committee of Fribourg University and Hospital (Switzerland, 043/12-CER-FR).

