### Treatment assignment

Patient randomization will be performed after lesion preparation. Exclusion criterion is when the lesion cannot be treated with BVS (reference vessel diameter >4.0 mm). Randomization will be completed via computer-generated numbers. Allocation concealment will be kept in sealed envelopes containing a non-transparent pleated color sheet in which the etiquette for intervention is embedded. The investigator is responsible for enrolment and a study nurse will assign participants to either stent implantation. Only the outcome assessors and data analysts are blinded to the intervention.

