### Clinical follow-up

Patients will be followed clinically by clinic visits or by telephone interview at 3, 6, 9 and 12 months, and 2 and 5 years. No blinding will be present during the collection of outcome data. If the patient is not accessible, data can be retrieved from the referring physician or the hospital electronic database.

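### An unblinded principal investigator, kept informed of accruing clinical events, alone decides whether to halt the trial, while the DSMB only observes and informs

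*Protocol article*

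**What the plan says.** All references are to the protocol article.

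- **Who decides (Trial interruption).** "The principal investigator is continuously informed by the DSMB and CAEC and is, by not being blinded, solely responsible for trial halting".
- **Who watches (Trial interruption).** "The incidence of clinical events is under constant observation of the DSMB and CAEC".
- **When the trial halts (Trial interruption).** There are two rules. At the interim: "The trial will be halted should the incidence of clinical endpoints significantly differ between the different devices during the intermediate analysis". At any time: "The trial will also be halted should the incidence of adverse clinical events exceed the expected values at any point".
- **DSMB (Study design and overview).** "A Data and Safety Monitoring Board is responsible for safety and ethical aspects".
- **Adjudication committee (Study design and overview).** It adjudicates every reported event and also carries out the angiographic measurements. On its blinding: "All members of the CEAC are blinded to the primary results of the trial".
- **Blinding to device (Treatment assignment).** "Only the outcome assessors and data analysts are blinded to the intervention".
- **Collection of clinical outcomes (Clinical follow-up).** "No blinding will be present during the collection of outcome data".

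The committee's abbreviation is spelled CEAC in the design overview and CAEC under Trial interruption. I take these to be the same body.

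**The concern.** A monitoring board exists so that people who know the accumulating data by arm are not the people running the trial. Here the person who decides on halting is chosen because he or she is not blinded. That reverses the usual reasoning: knowing the treatments is a ground for keeping the halt decision apart from trial conduct. The rule is stated outright, so it is not a detail that a fuller protocol could be expected to supply.

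Three things are at stake:

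1. **The halt decision.** The article attaches no numerical limit to either rule. An article may leave that to the full protocol, but as written the rules leave room for judgement, and one informed person exercises it.
2. **The MACE composites.** Target-vessel and target-lesion revascularisation depend partly on clinical discretion, and the outcomes are gathered unblinded.
3. **The timing of the primary measurement.** An off-schedule angiogram done once six months have passed stands in for the nine-month one, so a decision to re-image early also fixes when late lumen loss is measured.

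**Working it through.** The plan gives no figure on this point to reproduce. The check is a comparison of sections.

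**Step 1. The decision path.** Design overview: the DSMB holds responsibility for safety. Trial interruption: the DSMB observes and informs, and the investigator alone halts. No section gives the DSMB a recommendation to make, or gives the Steering Committee a part in halting, although the design overview names that committee as supervising the trial.

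**Step 2. What the investigator is told.** The sentence on informing the investigator follows directly on the one about event incidence, so the content is clinical event data. Whether it is by device is not stated. The two rules differ:

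| Rule | Comparison | Needs by-device data? |
|---|---|---|
| At the interim | Between devices | Yes |
| At any point | Against expected values | No, pooled counts suffice |

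The sole decision-maker must therefore act on a between-device result at least once. No text limits what is passed on at other times.

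**Step 3. What the adjudication committee sees.**

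- Design overview: blinded to the primary results. The primary endpoint is late lumen loss, so this does not cover clinical events.
- Treatment assignment: outcome assessors are blinded to the intervention. The committee is not named, but it adjudicates events and measures angiograms, so it is naturally read as included.
- Trial interruption: the committee watches incidence constantly and reports to an unblinded person.

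These statements are compatible only if the committee works from pooled counts. The text does not say that it does.

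**Step 4. How much of the trial is exposed.**

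- Interim: 40 angiograms per group of a planned 80. Planned angiograms still to come = (80 − 40)/80 = 50% per group.
- Clinical follow-up runs to 5 years, which is 60 − 9 = 51 months beyond the nine-month angiogram.
- The substitution rule allows the primary measurement to fall up to 9 − 6 = 3 months early.
- Recruitment was complete as of November 2013 (Trial status). The exposure therefore concerns remaining angiograms, clinical follow-up and any halt decision, not further enrolment.

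**Step 5. Endpoint by endpoint.**

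- Revascularisation within MACE: exposed, because it is partly discretionary and collected unblinded.
- Halt decision: exposed, because one informed and unblinded person makes it.
- Late lumen loss: the reading is protected by blinded assessors and automated edge detection; the timing of an early angiogram is not.

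**The case against.** A board that advises a separate decision-maker is an ordinary arrangement, so the two accounts of the DSMB do not contradict each other. That stands. The complaint is about who the decision-maker is and what that person is told.

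The bias route is also partly assumed. The article does not say that the principal investigator treats trial patients or passes event data to those who do. Operators already know each patient's device, and outcomes are collected unblinded anyway, so what matters is the added effect of knowing aggregate figures. This limits the size of the concern but does not remove it: the halt decision is exposed whoever treats the patients, and in one centre the distance between investigator and operators is short.

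A reader might infer more than the document supports:

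- **That the investigator continuously receives comparative or late-lumen-loss results.** The text speaks of event incidence and does not mention a split by device.
- **That the adjudication committee cannot be both a monitor and blinded.** It can, on pooled counts, and the rule that applies at any time needs nothing more. What is shown is an ambiguity.
- **That the committee is declared blinded to both device and results.** No single section says so. The two statements come from different places and cover different things.
- **That assessor blinding is the trial's sole safeguard.** The article also states computer-generated randomisation, sealed envelopes, blinded analysts, angiography in all patients, automated measurement and analysis by intention to treat.
- **That the bias can be expressed as a relative risk.** This would need an assumed event rate and an assumed number of extra revascularisations. The article gives neither for this trial; its one MACE rate, 6.8% at two years, is quoted from an earlier study of the scaffold.

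**Conclusion.** The point holds on the stated text: sole halting authority rests with an unblinded investigator who is continuously informed of clinical events, and the DSMB has no recommending role. This should be changed. Confidence is high on that part. It is moderate on the adjudication committee, where the finding is only that three sections leave its blinding to device unclear while it monitors incidence.

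The magnitude is not estimable from the document. What can be said is where the exposure lies: half of the planned angiograms per group after the interim, revascularisation within the composites through five years, the timing of early angiograms, and the halt decision.

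The conclusion assumes that the two abbreviations denote one committee and that no restriction on reports to the investigator stands in a document not shown. If a charter already keeps by-device data from the investigator, the article's wording still needs correcting, but the practical risk is smaller.

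**What to change.** Reword Trial interruption, and align Study design and overview and Treatment assignment with it:

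1. Accumulating data by device go to the DSMB only.
2. The DSMB sends the Steering Committee a recommendation to continue, modify or halt, without comparative figures.
3. The Steering Committee decides. Its membership is not given in the article, so state that the principal investigator is recused from this decision if a member; otherwise the exposure would only move.
4. The adjudication committee passes adjudicated events to the DSMB, sees pooled counts only, and is named explicitly as blinded to device.
5. The principal investigator receives the recommendation and nothing more from the monitoring process.

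This is a governance change. It leaves the content of the two halting rules untouched and uses bodies the article already names. The cost is charter and protocol wording, and one extra step before a halt takes effect. With recruitment complete, it can protect only the follow-up and decisions still to come. For what has already happened, the trial report should state what event data the investigator received and whether they were by device.

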## Discussion

Although DES have revolutionized percutaneous coronary interventions by significantly reducing clinically relevant restenosis and ‘target-lesion’ revascularization [17-20], numerous reports have since demonstrated an increased incidence of late stent thrombosis (LST) [21-23]. This is primarily due to a hypersensitivity reaction with secondary delayed arterial healing [24,25]. Substantial efforts have been made during the last decade to develop bioresorbable materials such as transient polymers or temporary ‘scaffolds’. The rationale for creating such devices was to lower both the neointimal proliferation in the short term and the hypersensitivity reaction (leading to late stent thrombosis) in the long term. Ideally, the device would offer an acute transient radial strength and later be completely absorbed thereby restoring vascular physiology.

Several DES using bioresorbable materials are currently available. The most used and studied so far is the Biomatrix™ BES. BES is a metallic stent that uses an abluminal bioresorbable polymer coating. This polymer is completely converted to lactic acid by 6 months and, via the Krebs cycle, to carbon dioxide and water by 6 to 9 months. More recently, a fully bioresorbable coronary scaffold has been launched for clinical use. The Absorb™ BVS is the first, fully bioresorbable coronary scaffold to have been launched for clinical use with CE approval. It uses a poly-l-lactide polymer that undergoes a four-stage bioresorption through hydration, depolymerization, polymer fragmentation and dissolution over 2 years via the Krebs cycle [26]. BVS was chiefly used in simple patients and lesions during early phases trials (ABSORB cohort A and B; ABSORB EXTEND). A second-generation device was developed to overcome the initial limitations of early scaffold shrinkage and provide greater radial support. Putative advantages over conventional DES are early restoration of physiological processes, namely vasomotion and remodeling, superior conformability, beneficial edge-vascular response and suppression of late-stent malapposition [27]. BVS absorption and vascular remodeling seem to seal stable plaques in settings of stable angina and type A lesions. With its widespread clinical launch in 2012, little is known on the broader use in more complex cases or acute coronary syndromes. The use of the BVS in complex situations makes sense however, as the risk of long-term complications from conventional DES implantation is even higher (longer lesions, chronic total occlusion, acute coronary syndromes and so on). For the time being, evidence has only provided information on its non-inferiority to modern DES in very specific settings. The EVERBIO II trial will assess BVS efficacy compared to the latest DES on the market in all patients viable for inclusion experiencing more complex lesions and clinical situations.

## Trial status

The recruitment phase is complete as of November 2013.
